### Primary outcome measurement

#### VAS

Pain intensity will be assessed using a10 cm VAS of subjective pain assessment. Each patient will rate their pain on a scale of 0 to 10 (0 being an absence of pain and 10 being the worst pain imaginable)
[18,19]. VAS measurements will be made at baseline, and at one, three and five weeks. Our primary end point is three-week VAS.

### Secondary outcome measurements

#### PainVision

PainVision is a system used for the quantitative analysis of perception and pain; it has recently been introduced in the field of pain and anesthesiology
[20,21]. The PainVision system consists of four devices: (1) the main PainVision system unit, (2) a personal computer connected to the PainVision system, (3) sensors, and (4) a printer. The specific protocols for using the systems are as follows
[22]: first, sensors that transmit an electric current will be attached to the right medial forearm. The current perception threshold that indicates the pain threshold of each subject will be measured three times, and the mean values will be used for analysis; Second, the pain compatible electrical current will be measured by a gradually increasing pulsed current applied to the right medial forearm. The pain due to spondylolisthesis and the magnitude of electric stimulation are believed equal. The pain-compatible electrical current will be measured three times, and the mean values will be used for analysis. On the basis of these measurements, pain intensity will be calculated using the following equation:

$$\begin{array}{ll} \;\text{Pain intensity}=100 & \times \left(\text{pain}‒\text{compatible eletrical current}\right)\\ & \;\left(‒\text{current perception threshold}\right)\\ & \;/\text{current perception threshold} \end{array}$$

### SF-MPQ

The SF-MPQ, a shorter version of the MPQ, is a multidimensional measure of perceived pain in adults with chronic pain
[23,24]. The main component of the SF-MPQ consists of 15 descriptors (11 sensory, 4 affective) from the original MPQ. The descriptors are rated on an intensity scale as 0 = none, 1 = mild, 2 = moderate, or 3 = severe. The SF-MPQ also includes the Present Pain Intensity (PPI) scale. The PPI scale is a measure of the magnitude of pain experienced by an individual and a numeric-verbal combination that indicates overall pain intensity and includes 6 levels: 0 = none, 1 = mild, 2 = discomforting, 3 = distressing, 4 = horrible, and 5 = excruciating
[25]. Higher numbers indicate more severe pain. The SF-MPQ will be measured at baseline and at one, three and five weeks.

### ODI

The ODI is one of the most frequently used tools for measuring disability related to low back pain
[26]. The ODI contains 10 questions about daily activities, including inventories of pain intensity, personal care, lifting, walking, sitting, standing, sleeping, sexual life, social life, and traveling. Each question is rated on a scale from 0 to 5 points. The ODI scores range from 0 to 50. Higher scores indicate greater disability. The validated Korean version of the ODI
[27] will be measured at baseline, and at one, three and five weeks.

### Safety

We will confirm the safety of acupuncture by determining the red blood cell (RBC) count, hemoglobin level, platelet count, mean corpuscular volume (MCV), mean corpuscular hemoglobin (MCH), mean corpuscular hemoglobin concentration (MCHC), hematocrit (Hct), total white blood cell (WBC) count, erythrocyte sedimentation rate (ESR), aspartate aminotransferase (AST), alanine aminotransferase (ALT), serum urea nitrogen (BUN), creatinine level, serum sodium level, serum potassium level, and serum chloride level. All patients were evaluated two times, including the screening visit and after the termination of acupuncture.

Any reported adverse events will be recorded throughout the study and vital signs will be monitored at each visit. The patients will be requested to voluntarily report information about adverse events, and the researcher will confirm the occurrence of adverse events through methods such as a medical interview. Details about adverse events, such as the date of occurrence, degree of adverse events, causal relationship with the treatment, other treatments or medications that are suspected to cause the adverse event, and treatment of the adverse event, will be recorded in detail.

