**Methods/Design:**

The study is a randomized controlled pilot clinical trial of five weeks duration. Fourteen patients will be recruited and randomly allocated to two groups: an acupuncture plus interlaminar epidural steroid injection group (experimental group), and an interlaminar epidural steroid injection group (control group). All patients will be administered an interlaminar epidural steroid injection once a week for three weeks (three injections in total), but only the experimental group will receive additional treatment with three acupuncture sessions a week for three weeks (nine acupuncture sessions in total). The primary outcome will be measured by the visual analogue scale (VAS). Our primary end point is three-week VAS. The secondary outcome will be measured using the PainVision system, the short-form McGill Pain Questionnaire, and the Oswestry Disability Index. Assessments will be made at baseline and at one, three and five weeks thereafter (that is, the five-week assessment will be made two weeks after treatment cessation).

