[11,12]. Leibing *et al.*[13], Haake *et al.*[14], and Brinkhaus *et al.*[15] all reported a significant difference in their primary outcome measures–Visual Analog scale (VAS), Roland Morris Disability Questionnaire, and McGill Pain Index. Witt *et al.*[16] also reported a significant improvement in pain, function, and quality of life after acupuncture treatment when compared to routine care, at three months. However, no published trials have evaluated the efficacy and safety of acupuncture in patients with low back pain due to spondylolisthesis.

In the evaluation of the clinical and radiographic result of the transforaminal lumbar interbody fusion in degenerative and isthmic lower-grade spondylolisthesis, there were 7.6% serious postoperative complications observed, which required operative revision
[17]. Acupuncture would be helpful in patients with spondylolisthesis as a safe conservative treatment without severe adverse events as can happen in some surgical procedures, such as transforaminal lumbar interbody fusion. The primary aim of this trial is to establish the feasibility of a randomized controlled trial and the safety of acupuncture for reducing low back pain due to low-grade spondylolisthesis and improving function compared with usual interlaminar epidural steroid injection.

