### Participants

One of the main objectives of this study is to provide an estimate of the sample size required for the full-scale randomized controlled clinical trial. We plan to recruit 14 patients into this pilot study. A target of 14 patients with spondylolisthesis has been set.

The inclusion criteria are that participants must: be aged 18 to 65 years, have Meyerding Grade I to II spondylolisthesis, have low back pain of at least one-year duration, be available for possible follow-up during the clinical trial, and provide written informed consent voluntarily.

The exclusion criteria are: cauda equina syndrome, persistently exacerbated symptoms, progressive neurologic signs (sensory or motor changes); previous spine surgery; senile dementia, impaired cognitive function or other cerebral disease, severe psychiatric or psychological disorders; severe, concomitant disease (neuromuscular scoliosis, neurodegenerative disease); all contraindications to corticosteroid injection (e.g., insulin-dependent diabetes); alcohol/drug abuse; significant renal or hepatic disease; pregnant, lactating or planning a pregnancy; hypersensitive reaction to acupuncture treatment; inability to comprehend or express oneself in the Korean language; an individual deemed to be ineligible by a physician; or refusal to participate in the trial or to provide informed consent.

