### Randomization

Patients will be randomized using a computerized random number generator by an independent statistician blinded to patient assignment. Block randomization will be performed once a participant is confirmed to be eligible and their written informed consent has been obtained.

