### Interlaminar epidural steroid injection

The lumbar interlaminar epidural injections will be administered by an anesthesiologist under fluoroscopy in a sterile procedure room in an outpatient pain management department. The lumbar interlaminar epidural space will be identified by the loss of resistance technique and by fluoroscopic visualization with confirmation with a non-ionic contrast medium. The epidural space will be entered at the level of spondylolisthesis or one space above/below the level of spondylolisthesis. After confirmation of needle placement, 10 mL mepivacaine hydrochloride 0.1% (preservative free) and 5 mg non-particulate dexamethasone will be administered by injection.

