### Data collection

In this study, the primary outcome will be measured by VAS. The secondary outcome will be measured by the PainVision system, the SF-MPQ and ODI. Both the primary and secondary outcomes will be measured at baseline, and at one, three and five weeks thereafter. The schedule of treatment and outcome assessments is presented in Table 
1.

**Table 1 T1:** Schedule of treatments and outcome measures throughout the trial

		**Baseline**	**Treatment period**									**Follow-up period**	
		**0 week**	**1 week**			**2 week**			**3 week**			**4 week**	**5 week**
Measures	VAS	√	√						√				√
	Pain Vision	√	√						√				√
	SF-MPQ	√	√						√				√
	ODI	√	√						√				√
	Safety	√							√				
**Treatments**	Interlaminar epidural steroid injection		√			√			√				
	acupuncture		√	√	√	√	√	√	√	√	√		

*ODI*, Oswestry Disability Index; *SF-MPQ*, short-form McGill Pain Questionnaire; *VAS*, visual analogue scale.

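### About seven patients exposed to acupuncture can describe its safety but cannot confirm it: no events in seven still leaves an upper 95% limit of 41%

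*Protocol article*

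**What the plan says.** The Safety section opens with "We will confirm the safety of acupuncture by determining the red blood cell (RBC) count, hemoglobin level, platelet count" and continues through red-cell indices, white cells, ESR, liver enzymes, renal markers and electrolytes. All patients have the panel twice: at screening and once acupuncture has ended. Table 1 marks safety at week 0 and week 3. The section adds adverse-event recording throughout the study and vital signs at every visit. The Statistical analysis section adds a chi-square comparison of adverse events.

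Safety is not a side issue. The last paragraph of the Background states the primary aim as establishing the feasibility of a randomized trial and the safety of acupuncture. Just before that it sets out the expectation: "Acupuncture would be helpful in patients with spondylolisthesis as a safe conservative treatment without severe adverse events".

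On size, the Participants section says "We plan to recruit 14 patients into this pilot study", and the abstract says "Fourteen patients will be recruited and randomly allocated to two groups". Both arms receive three epidural steroid injections; only the experimental arm receives the nine acupuncture sessions.

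**The concern.** Confirming or establishing safety is a claim about what the trial will show. To support it, a clean result would have to rule out rates of harm that matter. With about seven exposed patients, a clean result is likely across a wide range of true rates, so it separates safe from unsafe poorly.

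At stake is the conclusion on a primary aim. If no abnormality or event is seen, the stated aim invites the report that safety has been confirmed. That statement could then be carried into the full-scale trial that this pilot is meant to inform.

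**Working it through.** **Inputs**

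- Total sample: 14 (Participants). It is a pilot target with no event rate, precision or power behind it, so there is no figure of the plan's own to reproduce.
- Arms: two (abstract, Interventions). The ratio is not stated. The Randomization section says only "Block randomization will be performed once a participant is confirmed to be eligible", without block size or ratio. Assumption: 1:1, so 14 / 2 = 7 exposed. Range examined: 5 to 9.
- Confidence level: 95%, matching the 5% significance level in Statistical analysis. Sidedness is not stated, so both versions are shown.

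**Step 1. What no events in n patients rules out.** The exact (Clopper-Pearson) upper limit for 0 of n is 1 − 0.025^(1/n) two-sided and 1 − 0.05^(1/n) one-sided.

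For n = 7: 1 − 0.025^(1/7) = 41.0%, and 1 − 0.05^(1/7) = 34.8%.

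| Exposed | Two-sided limit | One-sided limit |
|---|---|---|
| 5 | 52.2% | 45.1% |
| 6 | 45.9% | 39.3% |
| 7 | 41.0% | 34.8% |
| 8 | 36.9% | 31.2% |
| 9 | 33.6% | 28.3% |

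Even if all 14 patients had received acupuncture, the limits would be 23.2% and 19.3%.

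**Step 2. How often a real hazard would go unseen.** The chance of no event in seven patients is (1 − p)^7.

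- True rate 5%: 0.95^7 = 0.70
- True rate 10%: 0.90^7 = 0.48
- True rate 20%: 0.80^7 = 0.21

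A harm affecting one patient in ten would be missed entirely about half the time.

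**Step 3. Whether the control arm rescues the claim.** At 7 v 7, Fisher's exact test needs 5 v 0 to fall below 0.05 (p = 0.021); 4 v 0 gives p = 0.070. Power for true rates of 5% v 30% is about 2%, and for 5% v 50% about 17%. For a continuous laboratory value, approximate power is Φ(d × √(7/2) − 1.96), where d is the mean difference in SD units. It reaches 80% at about d = 1.5. The comparison is free of steroid bias but detects only very large effects.

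**Step 4. Scale.** The number of event-free exposed patients needed for a one-sided 95% limit at or below a rate r is ln(0.05) / ln(1 − r), rounded up: 29 for 10%, 59 for 5% and 299 for 1%.

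**The case against.** The best defence is that this is openly a pilot, that small exposure comes with that, and that the opening verb can be read mildly. The same section uses it for checking whether a reported adverse event occurred. The document sets no rule by which a clean panel becomes a finding of safety. Nor does safety rest on blood tests alone, since adverse events and vital signs are collected as well.

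Part of this stands. That clean panels would be reported as proof is an inference from the stated aim, not a written rule, and the panel is one of several safety sources. But the Background makes establishing safety a primary aim, which the mild reading does not cover, and every safety source rests on the same seven or so patients. The pilot status itself argues for describing rather than confirming.

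A reader might infer stronger faults that the document does not support:

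- **Steroid confounding.** Both arms receive the same three injections and all patients are sampled, so the randomized comparison separates the steroid effect. What remains is poor precision.
- **A sample taken on treatment, at the third injection.** The text places the second sample after acupuncture ends. Table 1, as extracted, has the week-3 safety tick in the same column as the week-level VAS and ODI ticks. That supports week 3, not the injection day.
- **No time point for controls, or a missing week-5 check.** Table 1 sets week 3 without distinguishing arms. Two evaluations match two ticks, and adverse events are recorded throughout. Moving the sample to week 5 would give up detection at the end of treatment and is not needed.
- **The surgical figure as a benchmark.** The Background says "there were 7.6% serious postoperative complications observed, which required operative revision", but as motivation. The protocol never sets that rate as a standard for acupuncture, and a blood panel does not measure it.

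**Conclusion.** The concern holds as a point about the stated conclusion. With about seven patients exposed, a wholly clean result is compatible with a true rate of up to 41.0% (two-sided) or 34.8% (one-sided) for any given event or abnormality. The design can describe safety; it cannot confirm or establish it.

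This rests on one assumption, 1:1 allocation, and is not sensitive to it: with 5 to 9 exposed the one-sided limit stays between 45.1% and 28.3%. The limits assume complete follow-up; losses would widen them. The choice of tests, the timing of the samples and the use of steroid in both arms are not at fault here.

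**What to change.** 1. In the Background and the Safety section, replace confirming or establishing safety with: *describe adverse events and laboratory changes under acupuncture added to epidural steroid injection*. Make the same change to the aim in the abstract.
2. Report acupuncture-arm counts of adverse events and of laboratory abnormalities with exact 95% limits, including when the count is zero.
3. Present laboratory changes as the between-arm difference at the existing week-3 safety assessment.
4. State that no conclusion of safety will be drawn from this pilot.

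The price is a less favourable stated conclusion. Recruitment, visits, blood samples and Table 1 stay as they are.

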### Withdrawal and dropout

All patients will have the right to withdraw from the study at any time. Participation will be ended at any stage if the patient refuses to continue, withdraws their consent, or violates the inclusion or exclusion criteria or the trial protocol. The trial will be stopped if the principal investigator believes that there are unacceptable risks of serious adverse events.

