### Statistical analysis

The statistical significance level will be set at 5%, and the data will be analyzed using intention-to-treat and per protocol approaches. Data will be processed with the last observation carried forward method for the intention-to-treat analysis, and will be performed using IBM SPSS Win ver. 19.0 statistical software (IBM Co., Armonk, NY, USA).

All demographic and clinical characteristics of the subjects (such as sex, age, and weight) will be processed based on descriptive analyses. Quantitative data will be presented as average, standard deviation, median value, and range. Qualitative data will be presented as the frequency and percentage. The study will identify the comparative equivalence of demographic variables and clinical characteristics between the experimental and control groups.

In order to identify differences in VAS, PainVision scores, SF-MPQ and ODI scores between the experimental and control group based on time (baseline, weeks one, three and five), a repeated-measure twofactor analysis will be performed to identify differences between groups, differences within each group based on time, and the effects of the interaction of the variables based on group. If the interaction between group and time is statistically significant, the point at which the pattern of results between the two groups changes will be checked.

The Chi-square test will be used to compare groups and the incidence frequency of adverse events related to acupuncture and interlaminar epidural steroid injection.

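### Ending participation for any eligibility or protocol violation leaves the intention-to-treat analysis with no post-violation outcomes, only carried-forward early values

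*Protocol article*

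**What the plan says.** Under Withdrawal and dropout, the protocol article states: "Participation will be ended at any stage if the patient refuses to continue". The same sentence continues with the other triggers, so that participation also ends if the patient "withdraws their consent, or violates the inclusion or exclusion criteria or the trial protocol". Four triggers (refusal, withdrawn consent, an eligibility violation and a protocol violation) share one consequence. What ends is participation, not study treatment. There is no distinction between minor and major violations, and no provision for outcome assessment afterwards.

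Under Statistical analysis, "the data will be analyzed using intention-to-treat and per protocol approaches". On missing values: "Data will be processed with the last observation carried forward method for the intention-to-treat analysis".

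The section on the VAS says "Our primary end point is three-week VAS" and "VAS measurements will be made at baseline, and at one, three and five weeks". The Design section gives both arms three injections and the experimental arm nine acupuncture sessions as well. On size: "We plan to recruit 14 patients into this pilot study".

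**The concern.** An intention-to-treat analysis is meant to include the outcomes of randomised patients who did not follow the protocol. The withdrawal rule ends participation for those same patients. If the rule is followed as written, a violator's week-3 VAS is not collected even when the patient would have attended, and no later analysis can recover it.

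LOCF is a poor substitute here. At week 3 the value carried forward was taken either before treatment or early in a three-week course. It also sets the patient's later change to zero in the repeated-measures comparison of group and time.

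Three uses of the trial are affected:

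- the between-group comparison, which the Hypotheses section states as an efficacy hypothesis and which is tested at 5%;
- the variability of the VAS, which matters because the Participants section makes the sample size of the full-scale trial a main objective;
- the safety data, because a patient whose participation has ended may miss the post-treatment laboratory assessment and later adverse-event enquiry.

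**Working it through.** The plan gives no figure to reproduce: the target of 14 comes without an effect size, standard deviation, power or dropout rate. The check is therefore a side-by-side reading, followed by illustrations whose inputs are labelled.

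**Step 1. Follow one violator through the plan.** A patient violates the protocol after the week-1 assessment. Withdrawal and dropout: participation ends. Data collection and Table 1: the next outcome assessments would be weeks 3 and 5, but nothing says they are kept for someone whose participation has ended. Statistical analysis: the intention-to-treat data set carries the week-1 value to weeks 3 and 5. If the violation comes before the week-1 assessment, the baseline value is carried throughout. If it comes after the week-3 assessment, the primary endpoint is intact and only week 5 is imputed.

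**Step 2. Weight of one patient.** Input: 14 patients (Participants section). Assumption: 1:1 allocation, so 14/2 = 7 per arm. One patient ended before week 3 is 1/7 = 14.3% of an arm; two would be 2/7 = 28.6%.

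**Step 3. Occasions for a violation.** Inputs: nine acupuncture sessions in the experimental arm and three injections in the control arm (Design section). Assumptions: each occasion carries the same independent probability p of a violation that ends participation. The chance that participation ends is 1 − (1 − p)^m, with m = 9 or m = 3.

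| Assumed p | Experimental, m = 9 | Control, m = 3 | Expected patients of 7 (experimental vs control) |
|---|---|---|---|
| 1% | 8.6% | 3.0% | 0.6 vs 0.2 |
| 2% | 16.6% | 5.9% | 1.2 vs 0.4 |
| 5% | 37.0% | 14.3% | 2.6 vs 1.0 |

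The experimental arm's own three injections are left out; counting them separately would widen the gap. The values of p are assumed. Only the difference in the number of occasions is documented.

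**Step 4. What the imputation can do to the week-3 difference.** Assumptions: 7 per arm; experimental adherers have mean VAS 6 at baseline, 5 at week 1 and 3 at week 3; the control mean at week 3 is 4; k experimental patients are ended before week 3 and each would have had a real week-3 VAS of x. The per-protocol difference is 3 − 4 = −1.00. With v as the week-3 value used for the ended patients, the intention-to-treat difference is [(7 − k)·3 + k·v]/7 − 4.

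| k | LOCF from week 1 (v = 5) | LOCF from baseline (v = 6) | Real values, x from 2 to 6 |
|---|---|---|---|
| 1 | 23/7 − 4 = −0.71 | 24/7 − 4 = −0.57 | −1.14 to −0.57 |
| 2 | 25/7 − 4 = −0.43 | 27/7 − 4 = −0.14 | −1.29 to −0.14 |

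For k = 2 the extremes with real values are (15 + 4)/7 − 4 = −1.29 and (15 + 12)/7 − 4 = −0.14. The LOCF result does not respond to x at all: once participation has ended, the analysis holds no information on what happened to the violators.

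**The case against.** The strongest reply is that the article condenses a fuller protocol. It does not define a protocol violation, set an attendance threshold or say in so many words that measurement stops. A reader might infer that one missed acupuncture session leads to removal; the article does not say so, and that definition may well stand in the full document. This limits how often the rule can be said to bite. It does not remove the point, because the rule itself is stated positively, has no threshold, and on its ordinary meaning ends assessment along with treatment.

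A second reply is that the analysis is still intention-to-treat in membership. That is correct. A reader might infer that it collapses into the per-protocol analysis, or that the two will agree artificially. The documents do not support this: LOCF keeps each ended patient in the assigned arm and in the denominator, and in the assumed example the results differ (−1.00 per protocol against −0.43 or −0.14). What stands is narrower: the intention-to-treat set adds no post-violation information.

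Third, it would be tempting to say that removal depends on response, or that the bias favours one arm. Nothing in the article shows either. Nor are observed data discarded; the values in question are never collected.

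Fourth, a patient who refuses to continue may be refusing assessments too, so that loss need not come from the rule. The point therefore concerns eligibility and protocol violations.

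Finally, this is a 14-patient pilot of five weeks, which limits the consequences. But it states an efficacy hypothesis, tests at 5% and is meant to inform the size of a full-scale trial.

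**Conclusion.** The point holds in a limited form. As written, the withdrawal rule ends participation for the patients whose outcomes an intention-to-treat analysis most needs, and the plan replaces their week-3 VAS with a baseline or week-1 value. Under assumed 1:1 allocation, each patient ended before the week-3 assessment means that 14% of an arm has an imputed primary endpoint that might have been obtainable. The loss may be heavier in the experimental arm because that arm has nine additional sessions. How many patients would be affected, and which way the estimate would move, cannot be determined from the documents.

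The conclusion rests on reading the end of participation as the end of measurement, which no section contradicts, and on the rule being applied as stated. The change is worth making because it costs little, but the flaw does not invalidate the trial.

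**What to change.** In Withdrawal and dropout, separate deviating from or stopping study treatment from withdrawing from follow-up. State that every randomised patient is assessed at weeks 1, 3 and 5 for VAS, PainVision, SF-MPQ and ODI, and for adverse events, unless the patient withdraws consent to data collection or declines it. In Statistical analysis, state that eligibility and protocol violations serve only to define the per-protocol set. LOCF would then be needed only for values that truly could not be obtained.

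Whether study treatment continues after a violation remains a clinical decision outside this change.

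The cost is about one sentence of protocol text and the follow-up of a few patients at visits already in the schedule.
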